**App utilization pattern**				
	Intervention low users (uses app <4 days/week)	5	5	10
	Intervention users (uses app ≥4 days/week)	5	5	10
Total		10	10	20

### Follow-Up and Retention

#### Tracking Participant Follow-Up

All participants will be contacted before each follow-up study visit (ie, 13, 26, and 39 weeks after baseline). Multiple contact methods will be used for youth who are difficult to reach (eg, mail, alternate phone numbers, email, text message, Facebook). Participants will be asked whether or not messages can be left for each of the phone numbers that they provide. They will be informed that messages will not contain any information regarding the nature of the project.

#### Study Visit Management

The preferred time frame for all follow-up visits is within 4 weeks before or after the target study visit date. If the participant is unable to attend a visit within this time frame, the site staff will work with the participant to identify a day closest to the scheduled visit to perform the visit.

Participants in the intervention arm will be reminded by the Epic Allies app via a discreet phone notification (eg, “Your allies need you–log in to Epic Allies”) to log on to the app every week. If a participant does not log on for 4 weeks, study staff will notify site staff and ask that they reach out to the participant.

#### Completing Web-Based Computer-Assisted Self-Interviewing Surveys

CASI surveys will ideally be completed at the clinic site during each study visit. Participants will be provided with a quiet, private area to complete the survey. The survey may be completed on the participant’s smartphone, but a computer with Wi-Fi connection should be made available in case the participant prefers to complete the survey on a computer.

If a participant is unable to attend a follow-up study visit, the participant may complete the survey on his or her own. The survey should be completed within 4 weeks before or after the study visit target date. If a participant is unable to complete the survey within this window due to extenuating circumstances, the window may be lengthened to 7 weeks.

#### Data Security

##### Epic Allies App Data

Caktus Consulting Group will store app usage data on a secure Web server for the duration of the study. At the end of the study, Caktus Consulting Group will send app usage data to the study team, destroy the data on the server, and then shut down the server. Protected health information is neither collected nor stored on the Web server.

##### In-Depth Qualitative App Satisfaction Interview

For the in-depth qualitative app satisfaction interview with intervention arm participants, the audio recording as well as the transcript will be marked with the participant’s study ID only. Any identifying information mentioned in the interviews will be redacted in the transcripts, thus the transcripts will be deidentified. Both files will be uploaded and stored on a secure server.

### Data Analysis Study Objective 1: Efficacy

#### Sample Size and Power Estimates

We estimated a sample size of 200 as feasible enrollment. Power calculations are estimated to detect between-group differences in the primary outcome (viral suppression) in a parallel two-group repeated measures design with equal allocation, based on a generalized estimating equation (GEE) framework assuming an exchangeable covariance structure, measurements at 3 follow-up points, and correlation among same participant repeat measures (rho) of .4. For all estimates, we used a two-sided test of significance and an alpha level of .05. Assuming a 20% loss to follow-up, we will have 80% power to detect absolute differences in viral suppression of 16.3% between the intervention and control groups in the proportion of participants with viral suppression when the proportion in the control group is 27%.

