**Secondary study outcomes**						
	VL suppression defined as VL below the lower limit of detection in the 6-week window before the scheduled study visits	Chart review (any value in 6-week window before scheduled visit) OR laboratory value collected at study visit			X	<40 copies/mL or lower limit of detection for site-specific assay used to test the specimen
	Engagement in care	CASI survey	X	X	X	Completion of HIV-related care clinic visit in last 3 months
	ART uptake (for participants not on ART)	CASI survey	X	X	X	“Are you currently taking medication to treat your HIV (Y/N)?”
	ART adherence^a^ (for participants on ART)	CASI survey	X	X	X	(1) “How many times during the day has your doctor told you to take a dose of medicine (pills or other medicines) to treat your HIV?” and (2) “Thinking about the last 7 days, how many times did you miss taking a dose of pills?”[64]

^a^Outcome of >90% adherence is comprised 2 components (1) is the denominator, indicating the frequency of doses prescribed (multiplied x7 to represent total weekly doses); (2) is the numerator, indicating the number of times, total, a dose was missed.

**Table 2 table2:** In-depth qualitative app satisfaction interview enrollment.

Antiretroviral therapy (ART) experience at entry		New to care	ART nonadherent	Total

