#### Quantitative Data Analysis

We will compare within- and between-group differences in primary and secondary outcomes for each follow-up time period. The 13- and 26-week follow-up will be considered our primary endpoint for the primary outcome, thus *P* values will only be computed for these time periods for the primary outcome. *P* values will be adjusted for multiple comparisons using the Benjamini-Hochberg procedure [65]. Estimates for all outcomes will be presented with 95% CI. Intervention and control groups will be compared on baseline characteristics to assess balance. Patterns of missing data for our primary outcome of VS will be examined and baseline characteristics of participants with complete vs incomplete follow-up will be compared with assess nonresponse and attrition biases.

Intervention effects will be evaluated using an intention-to-treat (ITT) approach. The primary study outcome (VS, defined as the lower limit of detection of site assay) will be compared at 13, 26, and 39 weeks in the intervention and control groups using generalized linear models (GLM), which can be used for dependent variables with normal, binary, poisson, and negative binomial distributions. Link functions will be selected as appropriate based on the distribution of the dependent variable. We will apply the GEE extension of GLM to account for within-participant correlation associated with repeated measures. GEEs allow for inclusion of categorical and count-dependent variables and appropriate specification of working covariance structures for observations that are correlated within groups and across time. Fixed main effects parameters for study site and eligibility group will be fitted to data to account for the nature of the randomized design. Intervention efficacy will be assessed in terms of the main effect for overall group differences. Use of a GEE framework means that inference will be made to the marginal effect of the Epic Allies treatment on the outcome, averaged across the study population. Secondary analyses will be performed similar to the methods described above to identify potential mediators and moderators of the intervention impact on primary outcome.

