## Results

A total of 146 YMSM and YTWSM were enrolled in Epic Allies between September 2015 and 2016. Demographic characteristics of study participants are shown in Table 3. Although we estimated 200 as feasible for enrollment, study sites had fewer individuals eligible for participation in the study than expected. As a result, our ability to detect differences in our primary outcome (viral suppression) with 80% power assuming 20% loss to follow-up and the proportion of viral suppression in the control group is 27%, decreases by 3.1% (>16.3% to >19.4%).

**Table 3 table3:** Sample characteristics of Epic Allies study population by intervention arm. Q1: 25^th^ percentile. Q3: 75^th^ percentile.

Characteristic		Intervention (N=74)	Control (N=72)	Total (N=146)

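### The stated 80% power is right for a three-visit averaged test, but the primary endpoint is weeks 13 and 26 only, so the power statement and the primary analysis contradict each other

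*Protocol article*

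**What the plan says.** The Sample Size and Power Estimates section describes a "parallel two-group repeated measures design with equal allocation", analysed by GEE with an exchangeable covariance structure and "measurements at 3 follow-up points, and correlation among same participant repeat measures (rho) of .4". On error rate it says "we used a two-sided test of significance and an alpha level of .05". With 20% loss to follow-up and 27% suppression among controls, it gives 80% power for an absolute difference of 16.3 points. The sample size itself was not derived from power: "We estimated a sample size of 200 as feasible enrollment".

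The Results section reports the shortfall ("A total of 146 YMSM and YTWSM were enrolled in Epic Allies between September 2015 and 2016") and restates the detectable difference on the same basis, wording the change as "decreases by 3.1% (>16.3% to >19.4" percent.

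The trial has three follow-up visits, at weeks 13, 26 and 39. Table 1 marks viral suppression at weeks 13 and 26 as primary. The week-39 measurement is a separate row under secondary outcomes, with essentially the same definition: "VL suppression defined as VL below the lower limit of detection in the 6-week window before the scheduled study visits".

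The Quantitative Data Analysis section names weeks 13 and 26 as the primary endpoint, says that P "values will only be computed for these time periods for the primary outcome", and adjusts P values by Benjamini-Hochberg. Its next paragraph has the primary outcome compared at all three visits by GEE and judges efficacy by the overall group main effect.

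**The concern.** A power statement should describe the test that will decide the primary question. This one counts three measurements per participant, and the third can only be week 39, which Table 1 classes as secondary and for which no P value is planned. It also uses alpha .05 for a single test, although the analysis section adjusts several P values.

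These are the only power figures in the article, and the second tells readers what the shortfall from 200 to 146 costs. If the primary test is confined to weeks 13 and 26, both figures are too favourable. A reader of a null result would then credit the trial with sensitivity to smaller effects than it has.

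**Working it through.** **Inputs, all from the article.** Control proportion p1 = .27; loss 20%; rho = .4; two-sided alpha = .05; equal allocation. Analysable per arm: n = 200 × .8 / 2 = 80 as planned, and 146 × .8 / 2 = 58.4 as enrolled.

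**Formula.** With m exchangeable measurements, the variance of a participant's mean is multiplied by (1 + (m − 1)rho)/m:

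- m = 3: (1 + .8)/3 = .60
- m = 2: (1 + .4)/2 = .70
- m = 1: 1

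The effective n per arm is n divided by this factor. With p2 = p1 + D and p̄ = (p1 + p2)/2:

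- SE under the null (pooled): s0 = √[2 p̄(1 − p̄)/n_eff]
- SE under the alternative: s1 = √[(p1(1 − p1) + p2(1 − p2))/n_eff]
- Power = Φ[(D − 1.96 s0)/s1]

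**Reproducing the plan's figures (m = 3).** For N=200, n_eff = 80/.60 = 133.3, p2 = .433 and p̄ = .3515, so s0 = .0585 and s1 = .0576. Power = Φ[(.163 − .1146)/.0576] = Φ(.84) = 79.95%, and the detectable difference at 80% power is 16.31 points. For N=146, power at 19.4 points is 80.7% and the detectable difference is 19.2 points (19.5 with 57 per arm). With m = 2 the N=200 figure would be 17.7, and with m = 1 it would be 21.3. Three visits were therefore counted, and the arithmetic is sound on that basis.

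**One test averaging weeks 13 and 26 (m = 2, alpha .05).** For N=200, n_eff = 80/.70 = 114.3, s0 = .0632 and s1 = .0622. Power = Φ[(.163 − .1238)/.0622] = Φ(.63) = 73.6%. For N=146, n_eff = 58.4/.70 = 83.4 and power at 19.4 points is 74.3%.

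**Separate tests at weeks 13 and 26.** With m = 1 and no adjustment, power at a visit is 58.0% (N=200) and 58.7% (N=146). With two P values, Benjamini-Hochberg at .05 declares both significant if the larger is at most .05. Otherwise it declares only the smaller, if that is at most .025. This was simulated with 1,000,000 draws, the two z-statistics correlated .4 and the same true difference at both visits.

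| Primary test | Power at 16.3 points, N=200 | Power at 19.4 points, N=146 | Detectable at 80%, N=200 | Detectable at 80%, N=146 |
|---|---|---|---|---|
| Three-visit average | 80.0% | 80.7% | 16.3 | 19.2 |
| Average of weeks 13 and 26 | 73.6% | 74.3% | 17.7 | 20.8 |
| Adjusted, a given visit | 53% | 54% | 21.9 | 25.8 |
| Adjusted, at least one visit | 66% | 67% | 19.2 | 22.6 |
| Adjusted, both visits | 40% | 41% | – | – |

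All rows use the pooled null variance, because that is the version that reproduces 16.3. Unpooled and logit-scale versions move the two-visit power only within 72.7% to 75.6%.

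**The case against.** The strongest defence is the article's own second description of the analysis. It has the primary outcome compared at weeks 13, 26 and 39 by GEE, with efficacy judged by the overall group effect. An exchangeable three-visit GEE with rho .4 is the power calculation for exactly that test, and on that reading 16.3 and 19.4 stand. This part of the defence holds. A reader might infer that the sponsor miscalculated, or that the design simply lacks 80% power. The document supports neither inference without qualification: the arithmetic is right, and the power exists for one of the two analyses described.

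The defence does not remove the conflict. A single overall effect gives one P value that includes week 39. That cannot be squared with P values for weeks 13 and 26 only, with adjustment across several P values, or with Table 1's secondary label for week 39. A three-visit comparison could be read as estimates with confidence intervals at each visit, with P values at two of them. On that reading the stated power no longer applies.

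Two further points limit the consequence. Enrolment of 200 was set by feasibility and has closed at 146, so no sample size decision depends on the answer. The plan also promises 95% confidence intervals for all outcomes, which will show directly which effects are excluded, whatever the power statement says.

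**Conclusion.** The point holds as an internal contradiction that leaves the stated power attached to the wrong endpoint. The 80% applies only to a three-visit main effect, which Table 1 and the primary-endpoint sentence reject. No test confined to weeks 13 and 26 reaches 80% at the stated differences.

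The size depends on which test is primary. If the two visits are averaged, the loss is modest: about 6 percentage points of power and about 1.4 points of detectable difference (16.3 to 17.7 and 19.4 to 20.8). If the visits are tested separately with adjustment, the loss is larger. A reader might take the 53-54% for a given visit as the trial's power. The article does not support that, because it never says that success requires a particular visit. If significance at either visit counts, the figure is 66-67%.

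These results assume the article's rho of .4, 20% loss at every visit counted, a control rate of 27% throughout, and the same difference at each visit.

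**What to change.** In Quantitative Data Analysis, name one primary test. Then restate power in Sample Size and Power Estimates and in Results for that test, using the pooled variance throughout so that the figures are comparable:

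- **One test averaging weeks 13 and 26:** replace 16.3 with about 17.7 points (N=200) and 19.4 with about 20.8 points (N=146).
- **Separate adjusted tests at weeks 13 and 26:** say what counts as success. For a given visit, state about 21.9 and 25.8 points; for at least one visit, about 19.2 and 22.6 points.
- **Three-visit main effect:** the present figures may stay, but Table 1 must then include week 39 in the primary outcome, and the sentences on the primary endpoint and P values must be changed to match.

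The cost is wording only. Under the first two options the stated detectable difference becomes less favourable. No extra participants are needed.

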#### Quantitative Data Analysis

We will compare within- and between-group differences in primary and secondary outcomes for each follow-up time period. The 13- and 26-week follow-up will be considered our primary endpoint for the primary outcome, thus *P* values will only be computed for these time periods for the primary outcome. *P* values will be adjusted for multiple comparisons using the Benjamini-Hochberg procedure [65]. Estimates for all outcomes will be presented with 95% CI. Intervention and control groups will be compared on baseline characteristics to assess balance. Patterns of missing data for our primary outcome of VS will be examined and baseline characteristics of participants with complete vs incomplete follow-up will be compared with assess nonresponse and attrition biases.

Intervention effects will be evaluated using an intention-to-treat (ITT) approach. The primary study outcome (VS, defined as the lower limit of detection of site assay) will be compared at 13, 26, and 39 weeks in the intervention and control groups using generalized linear models (GLM), which can be used for dependent variables with normal, binary, poisson, and negative binomial distributions. Link functions will be selected as appropriate based on the distribution of the dependent variable. We will apply the GEE extension of GLM to account for within-participant correlation associated with repeated measures. GEEs allow for inclusion of categorical and count-dependent variables and appropriate specification of working covariance structures for observations that are correlated within groups and across time. Fixed main effects parameters for study site and eligibility group will be fitted to data to account for the nature of the randomized design. Intervention efficacy will be assessed in terms of the main effect for overall group differences. Use of a GEE framework means that inference will be made to the marginal effect of the Epic Allies treatment on the outcome, averaged across the study population. Secondary analyses will be performed similar to the methods described above to identify potential mediators and moderators of the intervention impact on primary outcome.

#### Missing, Unused, and Spurious Data

Several procedures will be used to conduct data analysis when data for either outcomes or baseline covariates are missing. The first step will be to assess the extent and pattern of missing data. If data are missing for only a few cases, then data analysis will be conducted only on study participants with complete data. If the pattern of missing outcome data is monotone, then inverse probability weighting will be performed to adjust the available data for loss to follow-up [66]. If substantial nonmonotone missing outcome data are present, then a multiple imputation approach will be used. Unused or spurious data will be documented and discussed when disseminating results of this study. Baseline covariates will be compared between participants with complete follow-up vs those who have incomplete follow-up in order to assess the presence of informative missingness.

### Data Analysis Study Objective 2: Acceptability, Perceived Impact, and Sustainability

#### Qualitative Approach

The interview and analysis structure will follow a phenomenological approach to optimize our ability to capture and understand the study’s experience-based topics of interest (eg, experience of HIV diagnosis and acceptance, experience of engaging with Epic Allies intervention and participants). Phenomenology is an ideal theoretical approach for this component as it is focused on describing both *what* a given group of participants experience and *how* they experience this particular phenomenon [67-69]. Data are presented through textual descriptions of the phenomena based on summaries of the experiences described by respondents. The composite descriptions offer an explanation of the underlying structure which exists across the participants’ experiences [69,70]. This will focus on individual and shared experiences and meanings.

#### Qualitative Data Analysis

For the analysis, process interviews will be transcribed and then we will begin with our a priori list of themes (experience using Epic Allies, recent ART adherence challenges, etc). Study team members will read all transcripts and identify emergent themes from participants’ experiences. These themes will be discussed as a group, and a final list of themes will be developed with brief descriptions, relationships between themes, and supporting quotes. For the qualitative research component, the Atlas.ti qualitative data analysis software (version 8, Scientific Software Development, Berlin, Germany) will be used to assist with theme identification and building, as well as coding textual data [69,71]. Coding and analytic activities will be discussed during weekly team meetings.

### Interim Analysis

No interim analysis will be performed for this study. The study team determined that this study does not involve greater than minimal risk (45 CFR Part 46.404 and 21 CFR Part 50.51). Participation in this study poses no more harm or discomfort to participants than they may experience in normal daily life or during routine physical or psychological examinations or tests.

### Protection Against Harms

All sites have specific policies governing the treatment of human subjects. These policies specify that medical and psychological assistance will be available in the immediate environment in the event a participant should experience any adverse reactions resulting from study procedures.

## Results

A total of 146 YMSM and YTWSM were enrolled in Epic Allies between September 2015 and 2016. Demographic characteristics of study participants are shown in Table 3. Although we estimated 200 as feasible for enrollment, study sites had fewer individuals eligible for participation in the study than expected. As a result, our ability to detect differences in our primary outcome (viral suppression) with 80% power assuming 20% loss to follow-up and the proportion of viral suppression in the control group is 27%, decreases by 3.1% (>16.3% to >19.4%).

**Table 3 table3:** Sample characteristics of Epic Allies study population by intervention arm. Q1: 25^th^ percentile. Q3: 75^th^ percentile.

Characteristic		Intervention (N=74)	Control (N=72)	Total (N=146)
**Classification strata, n (%)**				
	New to care	36 (49)	38 (53)	74 (50.7)
	Antiretroviral therapy nonadherent	38 (51)	34 (47)	72 (49.3)
**Study site, n (%)**				
	University of South Florida	19 (26)	11 (15)	30 (20.5)
	Stroger Hospital	9 (12)	14 (19)	23 (15.8)
	Montefiore Medical Center	15 (20)	15 (21)	30 (20.5)
	Tulane Medical Center	9 (12)	17 (24)	26 (17.8)
	University of North Carolina	22 (30)	15 (21)	37 (25.3)
**Age <18 years, n (%)**				
	No	71 (96)	66 (92)	137 (94.0)
**Age**				
	Median	22.0	21.0	21.5
	Q1, Q3	20.0, 23.0	20.0, 23.0	20.0, 23.0
**Gender identity, n (%)**				
	Male	69 (93)	67 (93)	136 (93.2)
	Transgender female	5 (7)	3 (4)	8 (5.5)
	Other	0 (0)	2 (3)	2 (1.4)
**Sexual identity, n (%)**				
	Gay	55 (74)	58 (81)	113 (77.4)
	Bisexual	16 (22)	11 (15)	27 (18.5)
	Other	3 (4)	3 (4)	6 (4.1)
**Hispanic or Latino ethnicity, n (%)**				
	Yes	17 (23)	12 (17)	29 (19.9)
	No	57 (77)	60 (83)	117 (80.1)
**Black or African American race, n (%)**				
	Yes	60 (81)	60 (83)	120 (82.2)
	No	14 (19)	12 (17)	26 (17.8)
**White race, n (%)**				
	Yes	10 (14)	6 (8)	16 (11.0)
	No	64 (86)	66 (92)	130 (89.0)
